##### Statistical analysis plan

All statistical analyses will be conducted using SAS software (version 9.4, SAS Institute, Inc. USA), with a two-sided *p*-value of <0.05 considered statistically significant. The primary analysis will be performed by intention-to-treat analysis. Descriptive statistical analysis will be first carried out to report baseline demographics, outcome variables, and other covariates at different follow-up time points, and then compared with Chi-square/Fisher exact probability tests (for categorical variables) or *t*-test/Mann Whitney U test (for continuous variables) between those who finish follow-ups and those who do not and between the mini-app group and the control group.

The preliminary efficacy of the min-app intervention to increase PEP initiation (any PEP initiation over follow-ups) will be evaluated using an unadjusted risk ratio. As for model acceptability, point estimates for a SUS score of ≥50 will be considered the minimum criteria for acceptability. Descriptive analysis will be used to evaluate model usability, including cumulative time to the mini-app, and time spent on specific components of the mini-app. Multiple imputations will replace missing data, and a sensitivity analysis will be performed to compare the multiple imputation analysis with the full case analysis.

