##### Sample size

Our previous study found that ~5% of MSM self-reported using PEP before the survey (36). A sample of ~400 participants (200 per group) would achieve 90% power to detect a moderate effect corresponding to a difference of at least 9% points (equivalent to a relative risk of 2.8 assuming a 5% prevalence of PEP usage in the control group) in PEP uptake between the intervention and control groups using a two-sided test at a 5% significance level and assuming a 10% attribution rate after 6 months. According to Cocks et al. (37) the sample size of a pilot trial should be at least 9% of that of the main planned trial. Hence, we plan to recruit 50 participants, 25 per group, to assess preliminary evidence for the further main study.

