##### Outcomes and covariates of the study

Primary and secondary outcomes, covariates, and specific survey time points for each variable in the pilot RCT are shown in Table 1.

**Table 1 T1:** Data collection and survey time points.

**Variables**	**Description/scale**	**Follow-ups (months)**			
		**Baseline**	**1**	**3**	**6**

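### Continuous secondary outcomes measured at baseline are compared between arms only by unadjusted two-sample tests, which are valid but give away precision at 25 per arm

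*Protocol article*

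**What the plan says.** All references are to the protocol article.

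- **Method.** The Statistical analysis plan section describes a first step in which baseline demographics are reported, together with "outcome variables, and other covariates at different follow-up time points, and then compared with Chi-square/Fisher exact probability tests" for categorical variables and a t-test or Mann-Whitney U test for continuous ones. The comparisons run "between those who finish follow-ups and those who do not and between the mini-app group and the control group". The section opens by setting the criterion for all analyses, "with a two-sided *p*-value of <0.05 considered statistically significant". It gives no other between-arm method for a secondary outcome.
- **Timing.** The section Outcomes and covariates of the study explains where the schedule is found: "Primary and secondary outcomes, covariates, and specific survey time points for each variable in the pilot RCT are shown in Table 1". That table schedules PEP knowledge, PHQ-9, the Zung anxiety scale and the five Levesque items at baseline and at months 1, 3 and 6. One Levesque item (intention to use PEP) has six points; the other four are yes/no.
- **Design.** Randomization is stratified by baseline HIV risk, low or high. The stratum appears in no stated comparison.
- **Size.** Under Sample size, "we plan to recruit 50 participants, 25 per group, to assess preliminary evidence for the further main study".
- **Primary efficacy.** PEP initiation is analysed once, over all follow-up, by an unadjusted risk ratio.

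**The concern.** When a scale is measured before randomisation and again afterwards, the baseline value usually predicts the later one. A two-sample test on the follow-up value alone leaves that predictable variation in the error term. With 25 per arm the intervals are wide to begin with, and the baseline values that could narrow them are already being collected.

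Testing at several visits also multiplies the p-values. No visit is named as principal and no rule says how the set of tests is to be read, although the section applies a 0.05 criterion throughout.

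The same sentence applies significance tests between arms to baseline demographics. After proper randomisation any such difference is due to chance, so these p-values answer no useful question. This does not extend to the comparison of completers with non-completers, which are not randomised groups.

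At stake is how informative the pilot's secondary estimates will be for planning the main trial.

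**Working it through.** **Inputs from the article.** 25 per arm (Sample size); two-sided 0.05 (Statistical analysis plan); three follow-up visits (Follow-ups); eight secondary measures, made up of three scales, one six-point item and four yes/no items (Table 1 and the outcome descriptions).

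**Input not in the article.** The correlation ρ between baseline and follow-up. Values of 0, 0.3, 0.5 and 0.7 are assumed.

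**1. The plan's own figure.** The only power statement concerns PEP uptake in the later main trial: "A sample of ~400 participants (200 per group) would achieve 90% power", with "equivalent to a relative risk of 2.8 assuming a 5% prevalence of PEP usage in the control group", "using a two-sided test at a 5% significance level and assuming a 10% attribution rate after 6 months". Taking 5% against 14%:

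n per arm = [1.960 × √(2 × 0.095 × 0.905) + 1.282 × √(0.05 × 0.95 + 0.14 × 0.86)]² / 0.09² ≈ 221

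That is 442 in total, or 492 after dividing by 0.9 for 10% loss. So 400 is not reproduced as a two-sided calculation; a one-sided 5% test gives 180 per arm, 360 in total and 400 after loss. This is a separate matter. No power or precision figure is given for the secondary scales, so there is none to reproduce on the present point.

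**2. Precision of one follow-up contrast.** Compared with the plain two-sample comparison, baseline adjustment changes the expected variance by

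VR = (1 − ρ²) × [1 + 1/(2n − 4)]

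with n = 25 per arm, so the bracket is 1 + 1/46 = 1.0217. The bracket is the cost of estimating the baseline slope under chance imbalance. Equivalent N = 50/VR. Power comes from the noncentral t distribution with noncentrality (0.5/√VR) × √(25/2), on 47 degrees of freedom adjusted and 48 unadjusted (where VR = 1).

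| ρ (assumed) | VR | Equivalent N | Effect detectable at 80% power | Power for 0.5 SD |
|---|---|---|---|---|
| Unadjusted | 1 | 50 | 0.81 SD | 41% |
| 0 | 1.0217 × 1 = 1.02 | 49 | 0.82 SD | 40% |
| 0.3 | 1.0217 × 0.91 = 0.93 | 54 | 0.78 SD | 44% |
| 0.5 | 1.0217 × 0.75 = 0.77 | 65 | 0.71 SD | 51% |
| 0.7 | 1.0217 × 0.51 = 0.52 | 96 | 0.58 SD | 67% |

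If the 10% loss assumed for the main trial also applied here (25 × 0.9 = 22.5, taken as 22 per arm), power for 0.5 SD would be 37% unadjusted, 46% at ρ = 0.5 and 61% at ρ = 0.7.

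The formula suits the three scales and, approximately, the six-point item. It does not carry over to the yes/no items. Any further gain from using all visits or the stratum is not counted, because the article gives nothing from which to size it.

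**3. Number of tests.** If each measure is tested at each follow-up, 8 × 3 = 24 tests.

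- Expected false positives with no effect anywhere: 24 × 0.05 = 1.2.
- Chance of at least one if independent: 1 − 0.95²⁴ = 0.71.
- Chance of at least one in a simulation of 24 correlated z-tests (assumed correlation 0.5 to 0.7 between visits and 0 to 0.5 between outcomes): about 47% to 66%.
- With one contrast per measure, if independent: 1 − 0.95⁸ = 0.34.

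**The case against.** The sentence is introduced as a descriptive step, and a condensed article may leave secondary-outcome models to a fuller document. In a randomised trial, unadjusted comparisons are unbiased and keep their error rate, and chance imbalance is already reflected in their standard errors. This is a pilot whose small sample the Discussion acknowledges, and no decision rests on a secondary p-value. The gain depends on an unknown correlation and is slight at 0.3. Adjusted logistic models for yes/no items could meet sparse cells at 25 per arm, where Fisher's exact test is defensible.

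Most of this stands and limits the point:

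- A reader might infer that the planned tests are invalid or biased. They are not; the loss is one of precision.
- A reader might take the 71% as the trial's false-positive risk. It requires 24 independent tests, whereas these are the same men at repeated visits on related measures.
- A reader might extend the precision argument to all eight measures. The formula does not support that for the four yes/no items.
- Testing separately at each visit is the natural reading of the sentence but is not stated in so many words.

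The argument from silence does not stand. The article names the tests, names the groups and sets a significance level, so the point concerns a method that was chosen and not a detail left out.

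**Conclusion.** The point holds as a question of efficiency for the continuous secondary outcomes with a baseline value: PEP knowledge, PHQ-9, Zung anxiety and, approximately, intention to use PEP. Baseline adjustment would cut the variance by about 7% at a correlation of 0.3, 23% at 0.5 and 48% at 0.7, against a loss of about 2% at zero. These figures assume a linear relation with similar spread in both arms and 25 per arm analysed.

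Multiplicity is a secondary consideration that depends on the each-visit reading. Between-arm baseline p-values are a reporting matter that alters no treatment estimate.

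A reader might infer that the pilot's main results are compromised. The documents do not support that: PEP initiation is a single risk ratio over all follow-up, and the System Usability Scale and exposure time have no baseline measurement. The change is worth making because it costs little, not because the present analysis is wrong.

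**What to change.** In the Statistical analysis plan section:

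1. Analyse each continuous secondary outcome with one baseline-adjusted model: ANCOVA at one visit, or a mixed model over months 1, 3 and 6 with arm, visit, arm-by-visit and the baseline value. Include the risk stratum as a covariate.
2. Name one principal time point, such as month 6. Report the adjusted difference there with its 95% CI, labelled exploratory.
3. For the four yes/no Levesque items, report the between-arm difference in proportions with 95% CI at the same time point, since adjusted logistic models may be sparse.
4. Present between-arm baseline comparisons descriptively, without p-values.

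On the natural reading this reduces 24 secondary between-arm tests to 8 principal estimates. Multiplicity is lessened but not controlled, so the exploratory label is still needed.

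The cost is a change of wording. Table 1 already collects the data and SAS 9.4 is already named. The statistical downside is the small loss of precision if the correlation is near zero.

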## Ethics statement

This study was approved by the medical institutional review board (IRB) of Binzhou Medical University (IRB No. 2021-007). All participants will sign an electronic informed consent form before enrolling in the study, which will also authorize access to their clinical records in the study hospitals. Each participant will be compensated 50 RMB each for completion of the baseline, 1, 3, and 6-month follow-ups. If the intervention proves to be effective, access to the invention is guaranteed for all high-risk MSMs even after the study has been concluded. We would also share the implementation challenges and successes in future research by reporting on international conferences and peer-reviewed articles.

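### With 25 per group and the plan's 5% control rate, the risk ratio chosen for PEP initiation has a zero denominator in about 28% of trials; a risk difference with a score-type interval would always be defined

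*Protocol article*

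**What the plan says.** The Sample size section fixes the pilot's size: "Hence, we plan to recruit 50 participants, 25 per group, to assess preliminary evidence for the further main study". The rates come from the calculation for the later main trial in the same section, which targets "a difference of at least 9% points (equivalent to a relative risk of 2.8", "assuming a 5% prevalence of PEP usage in the control group". The intervention rate is therefore 14%.

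The outcomes section makes PEP initiation the primary efficacy outcome. It is binary and taken from study-hospital records.

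The Statistical analysis plan section then does three things:

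- It states that preliminary efficacy "to increase PEP initiation (any PEP initiation over follow-ups) will be evaluated using an unadjusted risk ratio".
- It opens with a general criterion for all analyses, a two-sided p-value "of <0.05 considered statistically significant".
- It describes outcome variables at each follow-up and compares categorical ones between the two arms by chi-square or Fisher exact tests.

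The article names no measure of effect for PEP initiation other than the ratio, and it does not exempt the pilot's efficacy outcome from the p<0.05 criterion.

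**The concern.** A ratio of two proportions needs events in its denominator, and this pilot expects between one and two of them. If the control arm has none, the chosen measure is infinite or indeterminate. If either arm has none, the log ratio has no standard error. The investigators would then have to choose a continuity correction or another scale after seeing the data. If the control arm has one or two events, the ratio can be computed, but moving a single control participant changes it by a large factor.

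The pilot's stated purpose is to give preliminary evidence for the main trial. What is at stake is whether its headline efficacy figure can serve that purpose. A non-significant p-value, which is the expected result even if the planned effect is real, could also be read as evidence of no effect.

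**Working it through.** **Inputs.** 25 per group, control rate 5%, difference 9 points, relative risk 2.8 (all Sample size section); two-sided 5% criterion and unadjusted risk ratio (Statistical analysis plan section).

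**The plan's own figures.** 5% + 9 points = 14%, and 14/5 = 2.8, so the two forms of the effect agree. The article states no power or precision for 25 per group, so there is no pilot figure to reproduce. The main-trial total of about 400 is not used below.

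**Expected events.** Control: 25 × 0.05 = 1.25. Intervention: 25 × 0.14 = 3.5.

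**Chance that the ratio fails.**

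- No control events: 0.95^25 = 0.277.
- No intervention events: 0.86^25 = 0.023.
- At least one arm with none: 0.277 + 0.023 − 0.277 × 0.023 = 0.294.

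**What the ratio rests on when it is defined.** With Binomial(25, 0.05), P(1 event) = 0.365 and P(2 events) = 0.231, together 0.596. Given at least one control event, this is 0.596 / (1 − 0.277) = 0.82.

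**Sensitivity to the control rate.** The 5% is earlier self-reported PEP use, whereas the endpoint is initiation in hospital records during the study. The true rate could lie on either side. The rates other than 5% are assumptions.

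| Control rate | P(no control events) = (1 − p)^25 |
|---|---|
| 2.5% | 53% |
| 4% | 36% |
| 5% (plan) | 28% |
| 6% | 21% |
| 10% | 7% |

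**Two results close to expectation, on both scales.** The article names no interval method. A Wald interval on the log scale is used here for the ratio, and Newcombe's for the difference.

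- 4 versus 1 events: RR = 4.0. The standard error of log RR is √(1/4 − 1/25 + 1/1 − 1/25) = 1.08, so the 95% interval is 0.48 to 33. The risk difference is 12 points, interval −6 to +31.
- 4 versus 0 events: RR has no finite value. The risk difference is 16 points, interval −0.4 to +35.

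**What the p<0.05 criterion can deliver.** Exact enumeration of all 2×2 tables at 5% versus 14%, 25 per group, two-sided 5%:

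| Test | Power |
|---|---|
| Fisher exact | 5.5% |
| Uncorrected chi-square | 18.2% |
| Wald test on log RR | 0.8% |

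The average expected event count is (1.25 + 3.5)/2, about 2.4 per arm, which is too small to rely on the uncorrected chi-square. Fisher reaches p<0.05 only from 6 versus 0 or 7 versus 1 upwards; 5 versus 0 gives p = 0.0502.

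**The case against.** The strongest reply is that this is a pilot and says so. The article calls its efficacy aim preliminary in several places, concedes in the Discussion that the sample is relatively small, and calls for larger studies. Its power statement belongs to the main trial. This stands: low power at 25 per group contradicts nothing in the document and is not an error.

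A reader might infer that the ratio is the only efficacy comparison, so that over a quarter of trials would yield nothing. The document does not support this. The same section describes outcomes by arm and compares them by chi-square or Fisher exact tests, which remain available with no control events. What is lost is the effect estimate, since a test gives none.

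A reader might also infer that the Ethics statement, "If the intervention proves to be effective, access to the invention is guaranteed for all high-risk MSMs", hangs on p<0.05. It mentions neither a p-value nor the risk ratio, and the article sets no rule for progression to the main trial. That link would be conjecture.

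It can further be said that interval methods and zero-cell rules are commonly left to a full analysis plan. That is fair, and their absence is not the point here. The point is the choice the article does make, of a measure that is often undefined at these numbers.

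Finally, the risk-difference interval is also wide, and a change of scale adds no power. Both are true. The gain is an estimate and interval that exist whatever the counts.

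**Conclusion.** The concern holds as a point about the choice of effect measure, at moderate severity. On the plan's own 5% and 25 per group, the ratio has a zero denominator in about 28% of trials, and about 29% have a zero in one arm or the other. Most computable ratios rest on one or two control events. The 28% is conditional on the 5%: it falls to about 7% at an assumed 10% and rises to 53% at an assumed 2.5%.

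The p<0.05 criterion is uninformative for efficacy in this pilot, with Fisher power of about 5.5% at the planned effect. This is a reason to state that no significance claim is made, not a defect in the sample size.

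It would be too strong to say that the analysis cannot work. At 5% the ratio's denominator is non-zero in about 72% of trials, and the arm proportions and Fisher test are available in all of them.

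**What to change.** In the Statistical analysis plan section:

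- Report the two arm proportions and the risk difference in PEP initiation as the efficacy estimate, with a 95% score-type interval (Newcombe or Miettinen-Nurminen). This stays defined with zero cells and matches the 9-point effect in the Sample size section.
- Keep the unadjusted risk ratio as a supplement, given where it can be computed.
- State that the pilot's efficacy result is an estimate and that the p<0.05 criterion is not used to claim or deny efficacy.

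The cost is wording only; no data, participants or procedures change. The downside is that the headline leaves the relative scale that the Sample size section also quotes, and the interval will still be wide.

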#### Randomization

Simple randomization, stratified by baseline HIV risk assessment (low risk vs. high risk) will be performed once the baseline survey and HIV risk assessment are finished. An HIV infection risk assessment tool specifically designed for Chinese MSM was used in our study for HIV risk assessment (33). Variables included in the tool were the number of homosexual partners, HIV-positive homosexual partners, commercial male sexual behaviors, unprotected anal intercourse with men, diagnosis of sexually transmitted diseases, sex role during anal sex with a man, recreational drug usage, and group sex with men. All variables were reported for the previous 6 months. The total score in the tool ranges from 0 to 15, with scores of 5 and above being at high risk of HIV infection. The HIV infection risk assessment tool has been externally validated in different Chinses MSM groups and showed good discrimination performance for HIV infection risk (34, 35). Participants are finally assigned to the O2O-PEP or the control group in a 1:1 ratio with a computerized randomization algorithm by SAS 9.4. The computer-generated sequence will be generated by an independent statistician who is not involved in this study. After randomization, the participant will be automatically guided to the web link associated with their allocation. Study researchers and participants are both blinded to the allocation sequence.

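### Randomization is stratified by HIV risk but uses simple randomization, and the only efficacy estimate ignores the stratum; a stratified risk ratio should be specified

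*Protocol article*

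**What the plan says.** The Randomization section of the protocol article states: "Simple randomization, stratified by baseline HIV risk assessment (low risk vs. high risk) will be performed". The strata come from a score of 0 to 15, "with scores of 5 and above being at high risk of HIV infection". Allocation is "in a 1:1 ratio with a computerized randomization algorithm by SAS 9.4". No blocks or minimization are mentioned. Because randomization follows completion of the risk assessment, the stratum is known for every randomized participant.

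The Sample size section says "we plan to recruit 50 participants, 25 per group". The figures behind it are for a main trial, "equivalent to a relative risk of 2.8 assuming a 5% prevalence of PEP usage in the control group".

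Under Statistical analysis plan, the efficacy of the intervention on PEP initiation "will be evaluated using an unadjusted risk ratio", by intention to treat. The only sensitivity analysis described concerns missing data. Covariates are listed under Outcomes and covariates, but none enters the efficacy estimate.

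**The concern.** A factor chosen for stratification would normally be carried into the analysis. Here the design names one factor and the analysis drops it. The usual reassurance, that stratification has already balanced the factor, fails because simple randomization within a stratum is an independent coin toss for each man. Nothing forces the high-risk men to split evenly.

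If high-risk men take up PEP more often, an excess of them in one arm looks like an intervention effect, or hides one. The link is plausible: the score counts exposures such as unprotected anal intercourse and HIV-positive partners, which are the kind of event after which PEP is considered. The pilot's estimate is meant to inform the main study, and the estimator may well be carried forward with it.

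**Working it through.** **Inputs from the protocol.** 50 participants at 1:1; control uptake 5%; difference 9 points.

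**Assumptions, because the protocol gives neither.** High-risk share q of 30% or 50%; uptake in high-risk men 2, 4 or 9 times that in low-risk men, with the overall control rate held at 5%.

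**1. The plan's own figures.** 5% + 9 points = 14%, and 14/5 = 2.8, so the relative risk reproduces. The main-trial size does not. The plan says "A sample of ~400 participants (200 per group) would achieve 90% power", "using a two-sided test at a 5% significance level and assuming a 10% attribution rate after 6 months". The standard formula gives

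n = [1.96·√(2·0.095·0.905) + 1.2816·√(0.05·0.95 + 0.14·0.86)]² / 0.09² = (0.813 + 0.525)² / 0.0081 ≈ 221 per arm,

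or 221/0.9 ≈ 246 after 10% loss, against 200 stated. That is a separate matter. The pilot's 50 still exceeds 9% of 492 (about 45), and nothing below uses the 400.

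**2. How often the arms differ in risk.** With 25 per arm, the SD of the difference in high-risk share is about √(2q(1−q)/25): 0.130 at q = 30% and 0.141 at q = 50%. Simulation, which also lets arm sizes vary, gives 0.132 and 0.144. By the normal approximation:
- q = 30%: 0.15/0.132 = 1.14, one tail 0.128, so 26% of trials differ by 15 points or more.
- q = 50%: 0.15/0.144 = 1.04, one tail 0.149, so 30%.

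Simulation gives about 25% to 31%. With balanced allocation within strata the SD falls to 0.03 and a 10-point difference never occurs.

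**3. Shift in the risk difference under no effect.** Shift = (imbalance) × (high-risk rate − low-risk rate), where the low-risk rate is 0.05/(1 − q + q·g) for a g-fold gradient. Given an intervention-arm excess of 15 points or more, the mean imbalance is SD × φ(z)/(1 − Φ(z)): about 0.216 at q = 30% and 0.224 at q = 50%.

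| q | Gradient | Low / high rate | Shift |
|---|---|---|---|
| 30% | 2-fold | 3.8% / 7.7% | 0.0385 × 0.216 = 0.8 points |
| 30% | 9-fold | 1.5% / 13.2% | 0.1176 × 0.216 = 2.5 points |
| 50% | 2-fold | 3.3% / 6.7% | 0.0333 × 0.224 = 0.7 points |
| 50% | 9-fold | 1% / 9% | 0.08 × 0.224 = 1.8 points |

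Simulation gives about 0.8 to 2.6 points. In the same trials the Mantel-Haenszel risk difference averages about 0.

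**4. Shift on the ratio scale.** Over all simulated pilots, imbalance multiplies the unadjusted ratio, in either direction, by a median factor of 1.06 to 1.07 at a 2-fold gradient (95th percentile 1.21 to 1.22). At a 4-fold gradient the factor is 1.11 to 1.15 (95th percentile 1.40 to 1.51). The mean shift in log RR is zero.

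**5. The noise around it.** The SD of the risk difference under no effect is √(2·0.05·0.95/25) = 0.062. The shifts in step 3 are thus between about 0.8/6.2 = 13% and 2.6/6.2 = 42% of one SD. At 5% vs 14%, expected events are 1.25 and 3.5. The SE of log RR is √(0.95/1.25 + 0.86/3.5) = 1.00, and exp(1.96 × 1.00) gives a 95% CI spanning a factor of about 7 each way.

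**6. What stratifying does to precision.** For log RR at 50 participants, the SD is 0.715 to 0.733 by Mantel-Haenszel against 0.711 to 0.713 unadjusted (2- and 4-fold gradients). For the risk difference, the SD runs from about 1% worse to 6% better across the scenarios tried. At 400 participants the log RR figures are 0.376 to 0.383 against 0.383 to 0.384, a gain of at most 2%.

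**7. Whether a ratio exists at all.** P(an arm has no event) = 1 − (1 − 0.95²⁵)(1 − 0.86²⁵) = 1 − 0.723 × 0.977 = 0.29, and about 0.30 in simulation. In those pilots no risk ratio, stratified or not, is usable without a correction.

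**The case against.** Several points on the other side stand.

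- **The unadjusted ratio is not biased over randomizations.** Its standard error already covers chance imbalance. A reader might infer from the mismatch that the planned estimate is invalid; it is not. The displacement is conditional on the allocation that happens to occur, as with any unadjusted predictor.
- **The protocol does not show that risk group predicts uptake.** A reader might take the stratification factor to be the main driver of PEP use. The tool is described as validated for HIV infection risk, and no uptake by stratum is given. The Introduction puts PEP use at 4–6% among men with high-risk behaviours, while the Sample size section gives about 5% for MSM in another study. These are different sources and not a comparison of strata, but they lend no support to a steep gradient.
- **Sampling error dominates.** With about five expected events, no conclusion of a pilot seeking preliminary evidence would turn on this shift, and the Discussion admits the small sample.
- **The imbalance originates in the randomization.** If blocks within strata are intended, it nearly vanishes, and the unadjusted analysis is at most slightly conservative.

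One possible defence does not stand: that a condensed article simply leaves the detail to a fuller plan. The article names the estimator and calls it unadjusted, so this is a stated choice and not an omission.

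**Conclusion.** The point holds as a modest mismatch between design and analysis. Stratified simple randomization leaves chance imbalance in the high-risk share, and the only efficacy estimate stated does not account for it. How large the effect is depends on the assumed high-risk share and uptake gradient; with no gradient there is no shift at all.

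Two further inferences are not supported. One is that the risk difference should replace the risk ratio as the primary measure: nothing in the protocol argues against the ratio as the quantity of interest, only that it sometimes cannot be computed. The other is that adjustment would sharpen the pilot's estimate: it brings little or no gain in precision. The case for it is protection against an unlucky allocation, and consistency between how participants are randomized and how they are analysed.

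**What to change.** In the Statistical analysis plan section:

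1. Keep the risk ratio as the effect measure, but estimate it by Mantel-Haenszel stratified by the randomization factor (low/high HIV risk), with a 95% CI.
2. Report the Mantel-Haenszel risk difference with its 95% CI alongside, because it can still be computed when an arm has no events.
3. Show the unadjusted risk ratio as supportive.
4. State that the stratified analysis will carry into the main trial.

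In the Randomization section, state how balance within strata is to be achieved, or confirm that none is enforced.

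The cost is a sentence or two of wording and a stratified table in the SAS version already named. No new data are needed. The statistical price is at most a very slight loss of precision for the risk ratio in the pilot.
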